### Participants

#### Inclusion criteria

The patients to be included in the study should meet the following inclusion criteria:Patients with cervical spondylosis myelopathy, such as bilateral hand clumsiness and numbness, walking unsteady, weakness in the limbs, muscular dystrophy, increasing deep tendon reflex and positive Hoffmann and Babinski signs; the underlying diseases including multilevel cervical spinal stenosis, ossification of posterior longitudinal ligaments (OPLL), disc herniation, meeting operation indications: spinal neurological symptoms for at least 2 months, which are not cured by conservative treatment or in progression, significant spinal compression indicated by magnetic resonance imaging.Aged 18–84 years.Plans for receiving cervical decompressive surgery.A history of hypertension or office systolic blood pressure ≥140 mmHg on initial screening.Willing to participate in the study and sign informed consent.

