**Fig. 2 Fig2:**
[figure not shown]
Observation, assessment, and follow-up schedule

Eligible participants will be hospitalized for surgical treatment, and a pre-operation visit and clinical evaluation will be done before surgery, including antihypertensive medication, vital signs, physical examination, laboratory testing, spinal nerve function score and 24 h ABPM (Fig. 2). It is required that there is at least 3 days apart between initial screening visit and pre-operation visit. As soon as the operation condition is met, these subjects will receive cervical decompressive surgery, and their operation notes and adverse events will be recorded in detail.

All subjects will be followed up at 1 and 3 months after surgical operation, with antihypertensive medication recording, measurement of office blood pressure, 24 h ABPM and adverse events assessment collected at each time. In addition, VAS, physical examination and spinal nerve function score will be measured and collected at 3 month follow-up.

Regular antihypertensive medication therapy will be continued during the entire study period, however, the investigator can adjust the antihypertensive medication if necessary, according to treatment needs of individual patients.

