### Study endpoints

The primary endpoint is estimated as the difference between systolic ABPM before surgery (2^nd^ measurement) and the systolic ABPM at 1 month and 3 month post-operation (3^rd^ and 4^th^ measurement).

Four secondary endpoints were defined as: 1) The difference between diastolic ABPM before surgery and ABPM diastolic blood pressure at 1 month and 3 month post-operation; 2) control status of blood pressure at 1 month and 3 month post-operation (blood pressure control is achieved if systolic/diastolic blood pressure <140/90 mm Hg, reducing systolic blood pressure by >20 mm Hg or reducing diastolic blood pressure >5 mm Hg); 3) the use and dose adjustment of antihypertensive medication; and 4) the incidence of operative complications, including spinal nerve trauma, incision infection and fluid, pneumonia and urinary system infection etc.

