### Statistical analysis

Analyses will be made using SAS statistical software (version 9.3) by researchers at the Peking University Clinical Research Institute. The change in systolic ABPMs over the four times will be analyzed to observe the overall pattern of the blood pressure change in relation to the surgery, but the primary analysis will be the comparison of systolic ABPM between the 2^nd^ and 3^rd^, 4^th^ measurements (before and after the surgery). We will also calculate the regression-to-the-mean adjusted changes in systolic ABPMs as sensitivity analysis. Primary endpoint analyses and the change in systolic ABPMs over the four times will be carried out using analysis of covariance, as well as the first secondary endpoint (the change of 24 h ABPM diastolic blood pressure). Descriptive statistics will be used to summarize control status of blood pressure, the use and dose adjustment of antihypertensive medication and the incidence of operative complications.

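### Blood pressure control is scored after surgery with no pre-operative comparison, so some patients count as controlled even if surgery has no effect

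*Protocol article*

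**What the plan says.** Study endpoints lists "control status of blood pressure at 1 month and 3 month post-operation" as the second of four secondary endpoints. The level part of the definition is "blood pressure control is achieved if systolic/diastolic blood pressure <140/90 mm Hg". The same sentence goes on to "reducing systolic blood pressure by >20 mm Hg or reducing diastolic blood pressure >5 mm Hg". It does not say whether office or ambulatory pressure is meant, and it sets no condition on the patient's status before surgery.

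Inclusion criteria admits a patient with "A history of hypertension or office systolic blood pressure ≥140 mmHg on initial screening". These are alternatives, so a patient with a history needs no particular pressure at screening. The number of office readings is not given.

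Initial screening, assessment and follow-up schedules 24 h ABPM at screening, before the operation and at both follow-up visits. Follow-up comes "with antihypertensive medication recording, measurement of office blood pressure, 24 h ABPM and adverse events assessment collected at each time". Office pressure is named at screening and at follow-up. For the pre-operation visit only vital signs and ABPM are named. The same section says "the investigator can adjust the antihypertensive medication if necessary".

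Under Statistical analysis, the regression-to-the-mean adjustment is a sensitivity analysis of systolic ABPM change. For this endpoint the text is "Descriptive statistics will be used to summarize control status of blood pressure".

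**The concern.** The trial has no control group, so a percentage controlled after surgery has no reference unless the pre-operative data supply one. The definition asks only where the patient stands at follow-up. Two kinds of patient can therefore be counted as controlled with no effect of surgery:

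- a patient who read 140 or more at screening by chance and drifts back below it;
- a patient with known hypertension who was already below 140/90 before the operation.

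The Discussion relies on the repeated measurements to separate a surgical effect from regression to the mean. That protection is planned for the continuous systolic endpoint but not for this one. The Discussion also argues from a responder percentage in the group's earlier series (12 of 30, 40%). That outcome included stopping drugs and is not the same measure, but it shows how a post-operative control rate is likely to be read.

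**Working it through.** The article states no expected control rate, so it has no figure of its own to reproduce. The check asks how often a patient at or above 140 at screening falls below 140/90 later if surgery does nothing.

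**Inputs from the article.** Systolic limit 140 at entry; control limit 140/90; SD of change in 24 h systolic ABPM 15 mm Hg (Sample size calculation).

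**Assumed inputs.** If all the variance of change is visit-to-visit noise, the within-patient visit SD is 15/√2 = 10.6. This is an ABPM figure; using it for office readings is an assumption. Smaller values were also run. The population mean, between-patient SD and diastolic distribution are not in the article.

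**Model.** Each reading is the patient's true level plus independent visit noise. Select screening systolic ≥140, apply no treatment effect, and read later visits.

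**Hand check of one scenario** (mean 145, between-patient SD 12, visit SD 10.6):

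- Total SD = √(12² + 10.6²) = √256.36 = 16.01
- Correlation between visits = 144/256.36 = 0.562
- Cut-off in SD units = (140 − 145)/16.01 = −0.312; proportion selected = 0.623
- Mean of the selected, in SD units = φ(0.312)/0.623 = 0.380/0.623 = 0.610
- Expected fall with no effect = (1 − 0.562) × 16.01 × 0.610 = 4.3 mm Hg

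Simulation of the same scenario gives the same 4.3 mm Hg fall, with 24% below 140 systolic and 17% below 140/90 at one later visit.

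**Ranges over scenarios, no surgical effect, screening systolic ≥140:**

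| Assumptions | <140/90 at one visit | <140/90 at both follow-up visits |
|---|---|---|
| Mean 135–150, between-patient SD 12–15, visit SD 8–10.6; diastolic mean 85, between-patient SD 9, visit SD 6.4, true correlation 0.6 | 10–25% | 4–12% |
| Mean 135–155, between-patient SD 12–16, visit SD 7–10.6; diastolic mean 85, correlated visit noise | 7–29% | 2.5–15% |
| As the row above, also not <140/90 at the pre-operative visit | 5–20% | 1–8% |

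**What this means in patients.** With 20% drop-out, 50 × 0.8 = 40 patients are followed up. The share reading 140 or more at screening is unknown. If it is one quarter (10 patients), 10 × 0.07 to 10 × 0.30 gives about 1 to 3 controlled by chance. If it is three quarters (30 patients), the range is about 2 to 9.

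**Why the second pre-operative value helps.** In this model, once patients are selected on the screening reading, the second pre-operative reading and each follow-up reading have the same distribution when there is no effect. The expected proportion below 140/90 is then equal before and after (17% and 17% in the scenario above), and their paired difference is zero. The same comparison deals with history-route patients already below 140/90, because they count on both sides. Restricting the denominator to patients uncontrolled before surgery reduces chance responders but does not remove them (third row), since that restriction also selects on a noisy reading.

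**The case against.** A reader might infer that the control limit and the entry cut-off are the same test, taken once, so that the whole endpoint is an artefact of selection. The documents do not support that, for these reasons:

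- The text speaks of office systolic pressure at initial screening and does not say it is a single reading. If several readings are averaged, visit noise is smaller.
- The cut-off is one of two entry routes. Only patients without a known history are selected by it. For history-route patients, a high screening reading is not what admitted them, and noise within that route moves patients both ways across 140.
- The two limits are the same measure only if control uses office pressure. If ABPM is used, entry and outcome rest on different measurements and the link weakens.
- Control also requires diastolic pressure below 90, which has no counterpart at entry. The simulations include this.
- The 15 mm Hg belongs to ABPM, and the other inputs are assumed. The result spans about fourfold.

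All of these stand, and they limit the figure to a range for a subgroup. It is also fair that the endpoint is secondary and descriptive, and that the article concedes the limits of an uncontrolled design. An unseen analysis plan might add a denominator rule. However, the article itself defines the endpoint and its analysis, and as written a pre-operative reference is neither required nor reported.

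The two reduction limbs are a further source of chance responders. With the article's SD of 15, a systolic fall above 20 occurs in 1 − Φ(20/15) = 9.1% with no effect. With an assumed diastolic SD of change of 6 to 12, a fall above 5 occurs in 20% to 34%. Repairing those limbs would still leave the level limb without a pre-operative reference.

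**Conclusion.** The point holds in a limited form. The control endpoint is scored at each follow-up visit without regard to status before surgery, no pre-operative proportion is reported beside it, and the regression-to-the-mean adjustment does not reach it. With no surgical effect, roughly 7% to 30% of patients at or above 140 at screening would be below 140/90 at one later visit. This rests on assumed means and variances and on carrying an ABPM-based SD over to the screening reading. It is not an error rate for the whole endpoint, because the mix of entry routes and the measurement method are not known.

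The harm is to interpretation of one descriptive secondary endpoint. The primary comparison already uses the second pre-operative measurement as its reference and is unaffected. Nor do the documents show that control at both visits must replace the separate 1- and 3-month results. That would be a different endpoint, and it is better used as a supportive summary.

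**What to change.** In Study endpoints and Statistical analysis:

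1. Name one measurement method for control status that is available at all four visits. 24 h ABPM is scheduled at each; office pressure is not clearly scheduled at the pre-operation visit. The trial team should confirm that the stated limit is meant for the method named.
2. Report the proportion below 140/90 at the second pre-operative measurement beside the 1- and 3-month proportions, as paired within-patient differences with confidence intervals.
3. Report control achieved only among patients not below 140/90 at the pre-operative measurements.
4. Add control at both follow-up visits as a supportive summary, and keep the single-visit proportions.

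This takes a few sentences and no new visits or measurements. The cost is a smaller denominator and a lower headline rate for item 3, and a patient who misses a follow-up visit cannot be confirmed under item 4. The change does not separate surgery from changes in antihypertensive drugs, so these proportions should be read alongside the medication data already collected under the third secondary endpoint.

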## Discussion

The etiology and mechanism of essential hypertension remains unclear. Non-operative methods of essential hypertension treatment including antihypertensive pharmacologic drugs are still unsatisfactory [5, 8]. In the past several years, a new procedure named renal denervation had been shown to be safe and effective in controlling hypertension, supporting that the sympathetic nervous system (SNS) activity is critical in regulating blood pressure [6, 7]. Recently, we have proposed a novel hypothesis that cervical spondylotic myelopathy may be an important etiology of essential hypertension which has been termed as cervicogenic hypertension [13]. In our previous study, we found that the high blood pressure in 12 out of 30 (40 %) hypertensive patients was reduced to normal levels following the cervical decompressive surgery, which resulted in a termination of the antihypertensive medications. Furthermore, the high and unstable blood pressure in the other 15 patients became stabilized and was well controlled by antihypertensive drugs after cervical decompressive surgery [13]. Recently, Peng et al. reported two cases of cervical spondylosis with hypertension [15]. After anterior cervical discectomy and fusion, the blood pressure of both the two patients remain normal without hypertensive medications [15]. Also, we speculate that renal denervation only destructs the network of SNS, and that the diseased cervical SNS has a greater impact on initiating and increasing SNS activity, as it may be closer to central nervous system than the normal renal SNS.

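### The blood pressure control endpoint looks at pressure alone while drugs may be adjusted after surgery, so its rate cannot be read as an effect of surgery

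*Protocol article*

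**What the plan says.** All references are to the protocol article.

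- **Study endpoints.** The second secondary endpoint is control status at 1 and 3 months: "blood pressure control is achieved if systolic/diastolic blood pressure <140/90 mm Hg", followed by a systolic fall of more than 20 or a diastolic fall of more than 5 mm Hg. I read this as three alternative ways to qualify. The third secondary endpoint, listed separately, is "the use and dose adjustment of antihypertensive medication".
- **Initial screening, assessment and follow-up.** "Regular antihypertensive medication therapy will be continued during the entire study period", but "the investigator can adjust the antihypertensive medication if necessary, according to treatment needs of individual patients". No direction of adjustment is excluded. Antihypertensive drugs are recorded at the pre-operation visit and again at 1 and 3 months, at the same visits as the pressure measurements.
- **Statistical analysis.** Descriptive statistics are to "summarize control status of blood pressure, the use and dose adjustment of antihypertensive medication", together with operative complications. No combined measure is named.
- **Discussion.** In an earlier series, the high pressure of 12 of 30 patients "was reduced to normal levels following the cervical decompressive surgery, which resulted in a termination of the antihypertensive medications". Another 15 are described separately as well controlled on drugs. Fewer or lower-dose drugs are named as the expected benefit to patients. The limitations mention the absence of randomisation, placebo and Hawthorne effects, and regression to the mean, but not drug changes after surgery.

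**The concern.** The study is a single-group before-and-after comparison, and its stated purpose is to learn what the surgery does to blood pressure. A control rate after surgery helps with that only if the obvious competing cause of lower pressure, more antihypertensive treatment, can be separated out. The rule as written does not separate it: drugs may be changed and the score ignores the change.

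Inclusion adds to the exposure. A patient may enter on a single raised office systolic reading with no history of hypertension. If such a patient starts treatment after surgery, the response to the drug is scored as control.

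At stake is how a prespecified secondary endpoint is interpreted. A favourable control rate might be reported as evidence for surgery when part of it reflects prescribing.

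**Working it through.** **1. Apply the rule to four kinds of patient**, each uncontrolled before surgery.

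| Drugs after surgery | Pressure after surgery | Scored |
|---|---|---|
| Stopped | Below 140/90 | Controlled (first limb) |
| Drug added | Below 140/90 | Controlled (first limb) |
| Dose raised | Still 140/90 or above, systolic down by more than 20 | Controlled (second limb) |
| Dose raised | Still 140/90 or above, diastolic down by more than 5 | Controlled (third limb) |

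All four count equally. The difficulty affects every limb, not only the 140/90 threshold.

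**2. What two separate summaries can and cannot show.** Let C be the share controlled and I the share with any drug increase. The share both controlled and increased lies between max(0, C + I − 1) and min(C, I). Subtracting from C, the share controlled without an increase lies between C − min(C, I) and C − max(0, C + I − 1). The documents give neither C nor I, so the values below are assumptions.

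- C = 60%, I = 5%: controlled and increased, 0% to 5%; controlled without an increase, 55% to 60%.
- C = 60%, I = 40%: controlled and increased, 0% to 40%; controlled without an increase, 20% to 60%.

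The same bounds apply to drug reduction. With 60% controlled and 40% on fewer drugs, the share with both lies between max(0, 0.6 + 0.4 − 1) = 0% and min(0.6, 0.4) = 40%. With 70% and 40% it lies between 10% and 40%.

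**3. Does drug status change the meaning of such a rate?** The Discussion's own counts suggest so. Normal pressure with drugs stopped: 12/30 = 40%, as the article states (exact 95% interval 23% to 59%). If the 15 patients controlled on drugs would also meet the present rule, which is an assumption, a rule blind to drugs gives (12 + 15)/30 = 27/30 = 90% (73% to 98%). The gap is up to 50 percentage points. It is between control of any kind and control without drugs. It does not measure drug increases, because the article does not say that the 15 had any.

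**4. Precision of a joint proportion.** The plan enrols 50 and allows 20% drop-out, so 50 × 0.8 = 40 completers. The exact (Clopper-Pearson) limits for x of n are the 2.5% quantile of Beta(x, n − x + 1) and the 97.5% quantile of Beta(x + 1, n − x). For an illustrative 40%:

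- 16/40: 25% to 57%.
- 20/50 (no drop-out): 26% to 55%.

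Among patients treated before surgery the denominator will be no larger, so at the same proportion the interval will be at least about this wide. That is adequate for description.

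**The case against.** **The unseen plan may deal with it.** A condensed article need not list every table. The Statistical analysis section names the two endpoints in one sentence and does not rule out a cross-table. This stands as far as the missing table goes. It does not answer the definition: the rule for control is published in full and credits control obtained by adding drugs.

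**The drug endpoint already guards against this.** If few patients have drugs increased, the control rate can be distorted only slightly; with 5% increased, by at most 5 percentage points. That is right, and the two summaries should be read together. The protection weakens as increases become more common, as step 2 shows.

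**It is a secondary, descriptive endpoint.** Accepted; this limits the weight of the point. How drug changes affect the primary ambulatory systolic endpoint is a separate question.

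Three stronger readings are tempting, and the documents do not support them.

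- *That the study rests on normal pressure with drugs stopped.* The primary endpoint and the sample size rest on change in ambulatory systolic pressure. Drugs are to be continued, no withdrawal is planned, and the Discussion also treats control on drugs as a favourable result.
- *That the joint result is never estimated.* The article only fails to specify a joint measure. Both items are recorded at the same visits, so it can be derived.
- *That 12 of 30 is a benchmark to confirm or refute.* The article does not say that all 30 were on drugs beforehand, or when they were assessed. The denominators and time points may differ.

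**Conclusion.** The concern holds in limited form. The control rule uses pressure alone, drugs may be adjusted after surgery, there is no control group, and no joint summary is specified. The overall control rate therefore cannot be read as an effect of surgery.

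The size cannot be fixed from the documents because the share with drug increases is unknown. Under an assumed 60% control rate, the share controlled without an increase could be nearly the whole rate (55% to 60%, with 5% increased) or as little as a third of it (20% of 60%, with 40% increased). The conclusion rests on reading the three limbs as alternatives and on taking the permission to adjust drugs to include increases, which the text does not exclude.

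The flaw affects the interpretation of a descriptive secondary endpoint and leaves the primary test as it is. It is worth correcting because the correction is simple.

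**What to change.** In Study endpoints and Statistical analysis:

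1. Keep the overall control rate as defined.
2. At 1 and 3 months, also report control status cross-classified by antihypertensive drugs relative to the pre-operation record: none, fewer or lower dose, unchanged, more or higher dose. Apply this to patients qualifying by any limb, and show the limbs separately. Keep patients untreated both before and after surgery apart from those who stopped drugs. State in advance how substitutions and mixed changes are classed.
3. With exact confidence intervals, give (a) the proportion controlled without any increase in drug number or dose at each visit, and (b) the proportion below 140/90 on no drugs at 3 months among those treated before surgery.
4. Base any statement about control after surgery on these figures. Do not set (b) beside the earlier 12 of 30 as a like-for-like comparison.

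This removes one competing explanation only. Regression to the mean and placebo effects remain, and because no drug withdrawal is planned, (b) will also reflect decisions to stop treatment.

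The cost is one cross-table and one or two proportions per visit from data already collected, with no extra visits or patients. The small downside is a less favourable control rate.

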### Sample size calculation

Based on previous study which explored the efficacy of renal sympathetic denervation in treating hypertension, we assume that for the current study the primary outcome (the change of 24 h ABPM systolic blood pressure from pre-operation to the measurement at 3 months post-operation) has a standard deviation of 15 mm Hg [14]. We wish to be able to detect a difference of 11 mm Hg. Assuming a 20 % drop-out rate, a total of 50 participants are required to provide 90 % power, with the risk of two-sided type І error of 0.01.

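### The blood pressure control endpoint counts a diastolic fall of more than 5 mm Hg, or a systolic fall of more than 20 mm Hg, as control even when the pressure stays at or above 140/90

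*Protocol article*

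**What the plan says.** The second of four secondary endpoints (Protocol article, Study endpoints) is "control status of blood pressure at 1 month and 3 month post-operation". Its definition starts with a level, "blood pressure control is achieved if systolic/diastolic blood pressure <140/90 mm Hg", and then adds two changes: "reducing systolic blood pressure by >20 mm Hg or reducing diastolic blood pressure >5 mm Hg". These form one list of three items with a single final 'or', so each item is enough by itself.

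Four other places bear on how the rule works:

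- **Inclusion criteria.** The blood pressure requirement for entry is "A history of hypertension or office systolic blood pressure ≥140 mmHg on initial screening". It has no diastolic threshold.
- **Initial screening, assessment and follow-up.** Each follow-up visit includes "measurement of office blood pressure, 24 h ABPM and adverse events assessment collected at each time". Medication continues, and "the investigator can adjust the antihypertensive medication if necessary".
- **Sample size calculation.** The change in 24 h systolic pressure "has a standard deviation of 15 mm Hg". No SD is given for diastolic change.
- **Statistical analysis.** "Descriptive statistics will be used to summarize control status of blood pressure". No test or comparator is attached to this endpoint.

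**The concern.** Control describes the level a patient has reached. Two of the three routes describe how far the pressure moved and ignore where it ended. A patient can therefore be reported as controlled while above the article's own limit of 140/90. Because entry has no diastolic threshold, the diastolic route can also be met by lowering a diastolic pressure that was never raised.

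At stake is the meaning of the reported percentage. The study has no control group and this endpoint is only summarised, so the bare proportion at 1 and 3 months is the result. Part of it would consist of patients who are not below 140/90, and part would arise from ordinary visit-to-visit variation.

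**Working it through.** The article states no control rate or power for this endpoint, so there is no figure to reproduce. The check has two parts: the logic of the rule, and an illustration of its size.

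**1. Logic.** Let A = level below 140/90, B = systolic fall > 20, C = diastolic fall > 5. As written, control = A or B or C.

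Take a patient going from 165/75 to 165/69:
- A: systolic 165 is not below 140, so not met.
- B: the systolic fall is 165 − 165 = 0, so not met.
- C: the diastolic fall is 75 − 69 = 6 > 5, so met.

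The patient is reported as controlled. Entry is possible because office systolic pressure is at least 140, and the diastolic value of 75 plays no part in eligibility.

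**2. Chance of meeting each change route at one visit, with no true change.** For a normally distributed change with mean 0:

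- Diastolic: P(C) = 1 − Φ(5/SD). The SD is assumed to be 6–10 mm Hg.
  - SD 6: 1 − Φ(0.833) = 0.202
  - SD 8: 1 − Φ(0.625) = 0.266
  - SD 10: 1 − Φ(0.500) = 0.309
- Systolic: P(B) = 1 − Φ(20/15) = 1 − Φ(1.333) = 0.091. This borrows the SD of 15 from the sample size section, which refers to 24 h ambulatory pressure. The control definition does not say whether office or ambulatory pressure is used, so applying that SD here is also an assumption.

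**3. Share of controlled patients who are still at or above 140/90.** This was obtained by bivariate-normal simulation with no mean change, systolic SD 15, diastolic SD 6–10 and systolic/diastolic correlation 0.5–0.8. The share is P[(B or C) and not A] / P[A or B or C]. The baselines are assumed, because the article gives no baseline distribution.

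| Assumed baseline (mm Hg) | Share of 'controlled' patients not below 140/90 |
|---|---|
| 140/80 | 2–15% |
| 150/80 | 18–41% |
| 160/80 | 58–74% |

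At 160/80, about 9% of patients are below 140/90 by chance, while the rule as written reports about 22–34% as controlled.

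**The case against.** **Another reading of the sentence.** The sentence might be meant as a level below 140/90 together with one of the falls. The punctuation does not support that. It would also deny control to a patient who was already below 140/90 and stays there, and such patients can enter through a history of hypertension. If this was the intention, the sentence still has to be rewritten.

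**The diastolic route may add little.** A reader might infer that it dominates the endpoint. The article does not support this. Patients on continuing medication can enrol with pressure already near or below 140/90, and for them the level criterion does most of the work: at an assumed 140/80, 85–98% of those counted as controlled are below 140/90. Without a baseline distribution, which route contributes most is unknown. This part of the objection stands.

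**Other stronger readings that do not hold.**
- A reader might work out the chance of meeting the rule at either follow-up visit. The article does not say that either visit suffices, so only single-visit figures apply.
- A reader might set the new rate against the 12 of 30 patients in the Discussion whose pressure returned to normal. Those patients had stopped antihypertensive drugs, whereas here medication continues and may be adjusted. A rate based on 140/90 alone would not be comparable with it either.

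**Weight.** The endpoint is secondary, untested and openly defined, and its components can be recomputed from the planned measurements. This stands, and it limits the point to how the endpoint is defined and labelled.

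**Conclusion.** The point holds as a definition problem. As written, the rule reports some patients as controlled whose pressure is at or above 140/90, including patients whose diastolic pressure was never high. That conclusion follows from the text alone and needs no assumption.

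The size does rest on assumptions: no true change, normality, a diastolic SD that the article does not give, the sample-size SD carried over to this endpoint, an assumed correlation and assumed baselines. Under these, the diastolic route is met by chance about two to three times as often as the systolic one (0.202/0.091 = 2.2 to 0.309/0.091 = 3.4). The contamination of the control rate ranges from slight to more than half, depending on baseline pressure. No single figure within that range can be claimed.

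The primary endpoint and the diastolic change endpoint are not affected.

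**What to change.** In Study endpoints, define control status at each follow-up visit as pressure below the article's own 140/90 level, and nothing else. Report the proportion with a systolic fall above 20 mm Hg and the proportion with a diastolic fall above 5 mm Hg as two separate items under another name, such as 'response'. Do not merge them into the control rate.

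The fall proportions are worth keeping, because mean changes in systolic and diastolic pressure do not show how many patients had a given fall. A rate based on level alone still includes patients who were below 140/90 before surgery, so the pre-operative proportion can be shown beside it from measurements already planned.

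The cost is one sentence in the endpoint definition, with no new data. The downside is that the reported control rate will be lower.
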